#### RCT outcome measures

##### Primary outcome measure

The primary outcome is the number of days with heavy drinking, defined as four or more standard drinks (12 g alcohol/drink), measured by the timeline follow back instrument (TLFB) and AUDIT.

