### Statistical analyses and power calculation

The sample size has been estimated from the primary outcome variable, heavy drinking days during the past 30 days before baseline, at 3 months and at 6 months after baseline. Based on the assumption that the effect size of the intervention will be in the range of 0.4 SD in groupwise comparisons (alpha 5% and two-tailed tests) we need at least 98 individuals in each of the three treatment arms, and given an expected 25% dropout rate this motivates our choice of *N* = 375.

Data will be analyzed according to intention to treat (ITT). A secondary analysis will be per protocol for those participants who have contributed data at baseline and at 3-month follow-up. Primary and secondary outcome measures will be analyzed through ANOVA for repeated measures, with time (baseline, 3 months, and 6 months) as the dependent variable and type of intervention (TAU, or TAU + Glasklart, or TAU+ iBAC) as the independent variable.

A multiple regression analysis will be performed to investigate the extent to which the different predictor variables (consumption level and pattern, severity of dependence) contribute to the variation in the primary and secondary outcome measures.

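### The primary analysis mislabels time as the dependent variable, names a three-wave ANOVA that in standard form does not fit ITT, and calls a completer set per protocol

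*Protocol article*

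**What the plan says.** All the relevant statements but two are in the protocol article under Statistical analyses and power calculation.

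- Principle: "Data will be analyzed according to intention to treat (ITT").
- Method: "Primary and secondary outcome measures will be analyzed through ANOVA for repeated measures".
- Roles of the variables: "with time (baseline, 3 months, and 6 months) as the dependent variable and type of intervention" as the independent variable.
- Secondary set: "A secondary analysis will be per protocol for those participants who have contributed data at baseline and at 3-month follow-up".
- Sample size: it assumes that "the effect size of the intervention will be in the range of 0.4 SD in groupwise comparisons", with "alpha 5% and two-tailed tests", and needs 98 per arm. The total is then justified with the words "given an expected 25% dropout rate this motivates our choice of" N = 375.

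Under Primary outcome measure the article says: "The primary outcome is the number of days with heavy drinking, defined as four or more standard drinks (12 g alcohol/drink"). Under Procedure it says that participants' use of the devices is monitored throughout, as a means of improving adherence.

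**The concern.** The sentence on the ANOVA is the article's only specification of the primary analysis, and it gives the wrong role to time. In a repeated-measures ANOVA, time indexes the waves and the drinking measure is the response.

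The named method also sits badly with the named principle. Standard repeated-measures ANOVA works on complete rows, so a participant who misses one of the three visits leaves the analysis altogether. Someone seen at 3 months, the end of the intervention, but not at 6 months loses the 3-month value as well. In this population relapse could plausibly drive missed visits, so those excluded may differ from those kept. A result obtained in this way could be reported as intention to treat when it is a complete-case result.

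The per-protocol label has a similar problem. Readers will take it to mean the effect in people who followed the assigned treatment. As defined, it says only that two assessments were obtained.

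**Working it through.** **1. The plan's own sample size.** Inputs from the article: effect 0.4 SD, two-sided alpha 5%. Power is not stated in the article; I assume 80%.

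n per arm = 2 × (1.960 + 0.842)² / 0.4² = 2 × 7.85 / 0.16 ≈ 98.1

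This reproduces the stated 98 (99 if rounded up). The calculation is for a pairwise comparison of two arms.

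**2. How many a three-wave complete-case ANOVA keeps.** Inputs from the article: N = 375, dropout 25%. The article does not say which visit the 25% refers to. I take it as the share missing at least one visit, and assume equal allocation (125 per arm).

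- Kept: 375 × (1 − 0.25) = 281.25, about 281, or 93.75 per arm.
- Excluded: 375 × 0.25 = 93.75, about 94.

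If more people miss at least one visit (an assumed range):

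| Share missing a visit | Kept, total | Kept per arm |
|---|---|---|
| 25% | 281.25 | 93.75 |
| 30% | 262.5 | 87.5 |
| 35% | 243.75 | 81.25 |
| 40% | 225 | 75 |

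**3. What that does to pairwise power.** Power ≈ Φ(0.4 × √(n/2) − 1.96).

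- n = 98: 0.4 × 7.000 − 1.96 = 0.84, power 80.0%.
- n = 93.75: 0.4 × 6.847 − 1.96 = 0.78, power 78.2%.
- n = 75: 0.4 × 6.124 − 1.96 = 0.49, power 68.8%.

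At the article's own dropout rate the loss of power is small. The issue is who is analysed, more than how many.

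**4. The two analysis sets side by side.**

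| Set | Baseline | 3 months | 6 months | Device use |
|---|---|---|---|---|
| Standard repeated-measures ANOVA, labelled ITT | required | required | required | not considered |
| Per protocol as defined | required | required | not required | not considered |

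If the ANOVA is run in its standard form, everyone in the first set is also in the second. The set labelled ITT could then be no larger than the set labelled per protocol, which reverses the usual nesting. Separately, and whichever way the ANOVA is run, the per-protocol definition has no criterion on device use, treatment received or protocol deviation. A participant who never opened the app or the breathalyzer qualifies by attending two assessments.

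**5. The dependent variable.** The ANOVA sentence begins with the outcome measures as the thing analysed and ends with time in the dependent role. The outcome section names the number of heavy drinking days. Read together, the response is clear and the label on time is wrong.

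**The case against.** The strongest reply has four parts.

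*The dependent-variable wording is a slip.* This stands. A reader might infer that the planned model tests no treatment effect at all, because time would be regressed on arm. The article does not support that: the same sentence says the outcome measures are analysed, and the primary outcome is defined elsewhere. It is a mislabel to correct.

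*Listwise deletion is never stated.* This also stands. A secondary set limited to people with baseline and 3-month data makes most sense if the primary set was meant to include people without them. Estimation and imputation are commonly left to a statistical analysis plan, which is not shown here and could restore ITT. So it would be too strong to say that the trial cannot deliver an ITT comparison. What remains is that the method the article names does not, in its standard form, fit the principle it names.

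*Baseline as a wave need not weaken the test.* A reader might infer that the test is badly underpowered because a group effect averaged over baseline is diluted. The article never names that test, and with baseline as a wave the arm-by-time interaction is the natural one, so no such loss can be charged to the plan.

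*The bias is unknown.* Correct. Whether completers would understate or overstate the effect, and by how much, depends on how dropout relates to drinking in each arm and on correlations between visits. The article gives neither.

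None of these replies touches the per-protocol definition, which is written out in the article and is not left to another document.

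**Conclusion.** The point holds in three limited parts.

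1. Time is mislabelled as the dependent variable. This is an error of wording with an obvious correction.
2. Three-wave repeated-measures ANOVA in its standard form would analyse about 281 of 375 participants and leave out about 94. This assumes that 25% miss at least one visit and that no other missing-data method is used. It conflicts with the stated ITT principle unless another document says how the conflict is resolved.
3. The per-protocol set is a 3-month completer set. This needs no assumption, because it follows from the definition.

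It would go beyond the document to put a number on the bias or to claim a large loss of power. The case for change rests on the mismatch between label and method, which can be corrected cheaply.

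**What to change.** Replace the ANOVA sentence with text to this effect:

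> Heavy drinking days at 3 and 6 months are the dependent variable in a likelihood-based mixed model with arm, visit and arm-by-visit terms. Participants are analysed as randomised, with every available follow-up value. Efficacy is judged by the pairwise arm contrasts at follow-up, with [time point named by the sponsor] as primary.

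State how baseline enters, because the two usual options differ in whom they keep:

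- As a covariate: simple, but participants with no follow-up value add no information.
- As a wave with means constrained equal across arms: all randomised participants with a baseline value stay in the model.

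Pairwise contrasts also match the comparison on which the 98 per arm is based.

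Rename the baseline-plus-3-month set complete-case. If a per-protocol question is kept, define it from the device-use data already monitored.

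The cost is a change of wording in the protocol and analysis plan, and slightly more modelling. No new data or participants are needed. The downside is that the mixed model relies on data being missing at random given the observed values. If people drop out because of drinking that no visit recorded, it can still be biased.

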## Discussion

The high user degree of mobile phones, close to a 96% penetration rate worldwide, suggests a huge potential to reach populations with mobile technology [34]. In 2012 alone, a download of 40,000 different health-related apps was reported [21], a number most likely to be on a continuous rise. Thus, mobile phone technology is widely recognized as a potentially powerful tool for the prevention and management of disease [10]. Increased accessibility, real-time and ecological assessments, as well as high allowance for collecting sensitive information are some of the advantages of smartphone applications. There is, however, little research to provide evidence of its putative effectiveness [11, 12]. Few studies have been carried out, and criticism has been brought forth regarding small sample sizes, not considering possible biases and/or short follow-up times [18].

Improving ways of collecting data on alcohol consumption, as well as the treatment system, is of vital importance for the clinical practitioner as well as for the public health specialist. Today, there are uncertainties regarding reported levels of alcohol consumption for both total alcohol intake and pattern of drinking, and consequently also in assessing health effects of alcohol and in evaluating possible effects of treatment [22, 35]. Using digital technology has been shown to be effective not only in decreasing barriers for individuals to seek treatment but also with regards to the outcome of treatment, where it has been shown to be as effective as face-to-face alternatives [36]. Mobile phone technology has also been suggested as one means to offer time-efficient support within health care [37]. In conclusion, making use of novel technology within health care could be beneficial not only for the individual but also for society at large.

### Ethical considerations

Using apps which target the consumption of alcohol might be negative for some. One previous study suggests that male participants using the app “Promille-kollen” increased their drinking frequency and the authors speculated that use of a smartphone app might trigger men to compete with their peers in a competitive “drinking game” [38]. However, this study was in a university setting, enabling comparison between participants, while our study is in a clinical setting with individual participation only. Both apps used within our research project are developed by Med-tech companies specializing in e-health/m-health solutions for health organizations and other companies. Although in practice it would not only be possible but also very easy to make these apps publicly available for everyone to use (via App store or Google play), this will hardly be the case considering these developmental companies aim to make a profit. A possible future scenario is that m-health devices like these are made available via licenses that are procured by the healthcare systems. Currently, there are no ethical guidelines for mobile health applications (apps) despite the rapid innovation and use in the healthcare field. With regards to the suggested project, all collected data will be managed in a manner that is compatible with the security and personal data law. No personal data will be stored by Glasklart or iBAC, only a study number. Participation in the suggested study is considered not to present any risks for the patients; participation is voluntary and patients have sought treatment for their alcohol consumption.

This clinical trial will provide unique knowledge regarding the use of an application in a medical setting, by validating the app Glasklart and the breathalyzer iBAC as instruments for measuring alcohol consumption and, also, the possible effects that self-monitoring may have on the participants’ alcohol consumption behavior. The planned studies will also contribute information regarding how some possible app-specific features are perceived by the user, such as time-sensitive reminders, geolocation, and registering of mood and cravings when consuming alcohol. Possible implications for treatment of AUD will be discussed in future papers.

## Trial status

The trial is due to commence in 2018.

Protocol version 1, 31 May 2018.

Protocol amendments will be reported to the ISRCTN registry. http://www.isrctn.com/ISRCTN14515753

## Abbreviations

A-CHESS: Addiction—Comprehensive Health Enhancement Support System
AUD: Alcohol use disorder
BAC: Blood alcohol concentration
CRF: Case Record Form
CSQ: Client Satisfaction Questionnaire
HAD: Hospital Anxiety Depression Scale
ICC: Intra-class correlation
ITT: Intention to treat
LBMI-A: Location-Based Monitoring and Intervention for Alcohol Use Disorders
PEth: Phosphatidylethanol
RCT: Randomized controlled trial
SADD: Short Alcohol Dependence Data
SF-12: Short form Health Survey
TAU: Treatment as usual
TLFB: Timeline follow back
